### Statistics

3.10

After the intubation is complete, all data will be collected. Data analysis was performed using the statistical software SPSS 20.0. The thickness of the soft tissue in the front of the neck and clinical airway measurements will be compared between the “easy intubation” and “difficult intubation” group. ROC curves were used to determine the sensitivity and specificity of “difficult prediction capability” of each sonographic and physical measurements. Clinical factors associated with difficult intubation will be determined by univariate analyses. X^2^ analysis will be used for categorical or binary variables, unpaired t-test analysis was used for continuous variables. Multiple logistic regression analysis performed to determine independent predictors of difficult intubation. The results were averaged, and the data are presented as mean ± SD for each variable with continuous data. Categorical data were expressed as frequencies (%). All variables with P value along with their respective odds ratio and 95% confidence intervals were obtained. *P* value <.05 will be considered statistically significant.

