### Preoperative evaluation and ultrasonography

3.5

Preoperative evaluation and ultrasound examination were performed one day before the surgery, data was obtained in standard fashion. The patient's information, medical history was obtained. Physical examination include height, weight, body mass index (BMI). Airway evaluation include Mallampati score, neck mobility (flexion/extension degrees from midline), upper lip bite test, jaw movement, prominent incisor. A flexible ruler will be used to measure airway parameters, mouth opening (cm), thyromental distance (cm), sternomental distance (cm), hyomental distance (cm) and neck circumference (cm) at the level of the thyroid cartilage.

The thicknesses of the anterior neck soft tissues were measured with a portable ultrasound machine (M7 Super; Mindray, Shenzhen, China). A 6 to 13 MHz high frequency curvilinear ultrasound transducer was used for ultrasound scanning. Patients will be explained about the ultrasonography procedure and positioned in supine with the head in a neutral position. Ultrasonography with the probe placed in the transverse axis, craniocaudal sagittal scan, submental region of the neck. The distances were measured at five levels (hyoid bone, epiglottis, cricothyroid membrane, thyroid isthmus and suprasternal notch) with normal and extended neck position in the median axis. Figure 2A–E showed the ultrasonography procedure:

A.measure the distance from the skin to the hyoid bone;B.distance from the skin to the epiglottis performed at the thyrohyoid membrane level;C.distance from skin to anterior commissure of the cricothyroid membrane;D.distance from skin to thyroid isthmus;E.distance from skin to the trachea at suprasternal notch level. The images will be retrieved from ultrasound machine and stored on computer.

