### Sample size and study power

3.9

Optimal sample size has been evaluated based on a statistical power of 80% and a significance level of 0.05 (two-tailed). According to the previous study, in obese surgical patients, an incidence of difficult intubation was about 10% to 20%.^[16,17]^ Ultrasound measurements should predict at least 80% difficulty intubations (Cormack–Lehane grade ≥ 2b), additionally, 20 events are needed to derive two or more correlates in a logistic regression model.^[18]^ It is estimated that a sample size of 106 will be needed, to adjust the possibility 20% of dropout, 127 subjects will be recruited into the study.

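### ROC cut-offs would be chosen and scored on the same 11 to 21 difficult cases, so the reported sensitivity and specificity would be too high, most of all if the best of up to ten ultrasound distances is highlighted

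*Protocol article*

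**What the plan says.** All references are to the protocol article.

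- **Statistics (3.10):** "ROC curves were used to determine the sensitivity and specificity of" each sonographic and physical measurement. The section gives no threshold for any measure and describes no correction for choosing one from the data.
- **Outcome measures (3.4):** five ultrasound distances are listed together as primary, none ranked above the others. Ten clinical measures are listed as secondary.
- **Preoperative evaluation and ultrasonography (3.5):** each level is measured "with normal and extended neck position in the median axis", which makes up to ten distances per patient.
- **Study design (3.2):** one prospective cohort at one centre, with no separate validation sample.
- **Sample size and study power (3.9):** 106 evaluable patients, 127 recruited, and an assumed incidence of difficult intubation of 10% to 20%. It adds: "Ultrasound measurements should predict at least 80% difficulty intubations". No specificity is paired with that figure.
- **Objective (2):** the working hypothesis is that ultrasound beats traditional clinical tests on both sensitivity and specificity.

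**The concern.** An ROC curve offers a whole set of sensitivity and specificity pairs. It yields one pair only once a threshold has been picked. With no threshold preset and only one cohort, the threshold has to come from the patients who then score it. The chosen threshold fits the chance features of that sample, so the accuracy read off at that point is biased upwards. The bias is larger when events are few, and larger again when several candidate measures are compared and the best one is put forward.

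These are the numbers the study exists to produce. They answer the objective, and readers would set them beside the 80% in the sample-size section. A threshold whose sensitivity is overstated would miss more difficult airways in later patients than the report suggests. The Introduction itself links airway failure to maternal mortality.

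**Working it through.** **1. The plan's own figures.** The recruited number follows from 106 × 1.20 = 127.2, which gives 127 (dividing instead, 106 / 0.80 = 132.5, would give 133). The 106 does not follow from the stated inputs: 20 events at 10% to 20% incidence need 20 / 0.10 = 200 to 20 / 0.20 = 100 patients, and 106 implies an unstated incidence of 20 / 106 = 18.9%. The point here needs only the event count.

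**2. Expected events.** 106 × 0.10 = 10.6 and 106 × 0.20 = 21.2, so about 11 to 21. Section 3.7 (Laryngoscopy) withdraws patients with unanticipated difficult ventilation or intubation, which can lower this further.

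**3. Precision before any search.** Exact 95% intervals for an observed sensitivity near 80%: 9/11 = 82% (48% to 98%) and 17/21 = 81% (58% to 95%).

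**4. Assumptions for the size of the bias (not in the document).** Binormal measures, all with true AUC 0.70, and the cut-off that maximises the Youden index. Under this model the separation is √2 × Φ⁻¹(0.70) = 0.742, and the best true cut-off has sensitivity = specificity = Φ(0.742 / 2) = 0.645.

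**5. Effect of searching for one cut-off.** Probability that a single measure shows sensitivity of at least 80%:

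| Events | Cut-off fixed in advance (true sensitivity 0.645) | Cut-off searched in the same data |
|---|---|---|
| 11 | 0.19 | about 0.50 |
| 21 | 0.085 | about 0.36 |

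**6. Apparent against true sensitivity at the chosen cut-off.** N = 106, correlation 0.5, measure with the highest AUC selected:

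| Measures | Events | Apparent | True | Excess (points) |
|---|---|---|---|---|
| One | 11–21 | 72–75% | 60–62% | about 10–15 |
| Best of 5 | 16 | 78% | 60% | 18 |
| Best of 10 | 11 | 82% | 57% | 25 |
| Best of 10 | 16 | 80% | 60% | 20 |
| Best of 10 | 21 | 79% | 61% | 18 |

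The selected best-of-ten measure shows at least 80% in 54–67% of simulated studies. A single measure does so in 37–48%.

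**7. Sensitivity to the assumptions.** Selecting on the best Youden index and varying the correlation from 0 to 0.8, the best of ten shows 78–85% against a true 54–62%, an excess of 16 to 31 points, and reaches 80% in 52–78% of runs. Specificity is inflated much less (at correlation 0.5, 73% against 70% with 11 events and 71% against 67% with 21), because there are many more easy cases. With true AUC 0.60, the best-Youden measure of ten reaches 80% in 36–60% of runs.

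**8. The role of specificity.** A measure with AUC 0.70 can truly reach 80% sensitivity, but at specificity Φ(0.742 − 0.842) = 46%. If at least 80% sensitivity and at least 70% specificity are both asked for, at least one of ten measures shows this in 33–58% of runs with 11 events and 15–25% with 21 (AUC 0.70). With AUC 0.60 the figure is 1–11%.

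**The case against.** The strongest reply is that much of this rests on silence. Section 3.10 states no cut-off rule, does not say that a best level will be chosen, and does not rule out a correction. An analysis plan that is not shown could contain one. Part of this stands. That cut-offs will be derived is an inference, though a tight one, and selection of a best level is a possibility and not a stated step. But the method that is stated, followed as written, gives apparent accuracy, and even a single measure with no selection among levels is inflated. The limitations listed in the Discussion name selection bias and generalisability but not this.

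Three stronger readings are tempting, and the document does not support them.

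- *A mediocre measure is bound to show 80%.* It is not. A given measure does so in under half to about half of simulated studies, and the best of ten in somewhat more than half. It becomes near-certain (91–100%) only for the weaker event that at least one of ten reaches 80% sensitivity, whatever its specificity.
- *The bias favours ultrasound.* Seven of the ten clinical measures in section 3.4 are also continuous (BMI, neck mobility in degrees, mouth opening, three mental distances, neck circumference), and section 3.10 gives them the same ROC treatment. A net tilt is plausible only against graded tests such as Mallampati or upper lip bite, and it was not simulated.
- *The 80% is a success criterion.* It appears only as a planning figure for sensitivity. Nothing says that the study passes or fails on it.

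**Conclusion.** The concern holds in limited form. As planned, the sensitivity and specificity of every measure scored by a data-chosen cut-off will be optimistic, for ultrasound and continuous clinical measures alike. The direction follows from the design: no preset cut-off, one cohort and few events. The size rests on the assumptions in the working. With true AUC 0.70, a Youden cut-off and correlation of 0.5, sensitivity is about 10 to 15 points too high for one measure and about 18 to 25 points too high for the best of ten. A distance that truly detects about 60% of difficult cases is then more likely than not to show the 80% planning figure, but only if the best of ten is the one highlighted.

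**What to change.** 1. Bootstrap the whole procedure. Repeat the cut-off choice in each resample and, if a best level or neck position will be highlighted, repeat that choice too.
2. Report optimism-corrected AUC, sensitivity and specificity with 95% confidence intervals as the main figures, for ultrasound and clinical measures alike. Label in-sample values as apparent.
3. For clinical tests that have conventional cut-offs, fix those in advance.
4. Set the corrected sensitivity beside the 80% planning figure descriptively, together with its specificity. Do not make it a pass/fail test on the lower confidence limit. Even with an uncorrected sensitivity at a fixed cut-off, 16/16 detected has an exact lower 95% limit of 0.025^(1/16) = 79.4%, and 11/11 has 0.025^(1/11) = 71.5%.

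Naming one primary level and neck position and stating the cut-off rule in advance would reduce the problem further.

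The cost is extra analysis code and less favourable reported accuracy. No further patients or measurements are needed.

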### Outcome measures

3.4

Primary outcomes:

Ultrasound measurements: thickness of anterior cervical soft tissue at five levels: distance (cm) from skin to the trachea at hyoid bone, epiglottis, cricothyroid membrane, thyroid isthmus, suprasternal notch level.Cormack–Lehane grade

Secondary outcomes:

Body mass index (BMI), Mallampati score, neck mobility (flexion/extension degrees from midline), upper lip bite test, jaw movement, mouth opening (cm), thyromental distance (cm), sternomental distance (cm), hyomental distance (cm) and neck circumference (cm) at the level of the thyroid cartilage.

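### About 11 to 21 expected events cannot support a search for independent predictors among 15 to 20 candidates by ordinary logistic regression

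*Protocol article*

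**What the plan says.** Section 3.9 (Sample size and study power) takes its event rate from earlier work: "in obese surgical patients, an incidence of difficult intubation was about 10% to 20". It states "It is estimated that a sample size of 106 will be needed", inflates this to 127 for dropout, and adds that "20 events are needed to derive two or more correlates in a logistic regression model".

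Section 3.4 (Outcome measures) lists soft-tissue thickness at five levels as primary. The clinical measures are secondary, beginning "Body mass index (BMI), Mallampati score, neck mobility (flexion/extension degrees from midline), upper lip bite test, jaw movement, mouth opening (cm" and continuing with three mental distances and neck circumference, ten in all. Section 3.5 measures each ultrasound distance in two neck positions and also records prominent incisors.

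Section 3.10 (Statistics) says: "Clinical factors associated with difficult intubation will be determined by univariate analyses", by chi-square and t tests. Later it says: "Multiple logistic regression analysis performed to determine independent predictors of difficult intubation". The significance threshold is P<.05. The secondary objective in section 2 is whether the clinical screening tests are independent predictors of difficult airway.

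**The concern.** The sample-size section ties the logistic model to a small number of terms, whereas the analysis section sets the same model to work on a candidate list many times longer. With so few events, ordinary maximum likelihood picks different variables from sample to sample, and the variables that reach significance tend to be those whose effects happen to be overestimated. Many candidates are also likely to be correlated, such as BMI, neck circumference and thickness at adjacent levels, which makes their separate contributions harder to estimate.

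The secondary objective rests on this model. A paper that names independent predictors from it could put forward spurious or exaggerated airway tests for obstetric practice.

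**Working it through.** **Plan's own sample size.** 106 × 1.2 = 127.2, which matches the 127 to be recruited. The 106 does not follow from the stated inputs. Twenty events need 20/0.20 = 100 women, 20/0.15 = 134 or 20/0.10 = 200, and 106 appears only at an unstated incidence of about 19% (20/0.19 = 105.3, rounded up). That is a separate matter; the event count below takes 106 as given.

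**Expected events** = evaluable N × incidence (both from section 3.9).
- 10%: 106 × 0.10 = 10.6
- 15% (midpoint): 106 × 0.15 = 15.9
- 20%: 106 × 0.20 = 21.2

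**Terms supported.** Reading the rule in section 3.9 as 20 events for two terms gives 10 events per term, so the supported number is 10.6/10 = 1.1, 15.9/10 = 1.6 and 21.2/10 = 2.1 terms.

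**Candidates** (sections 3.4 and 3.5). 5 ultrasound + 10 clinical = 15. With both neck positions, (5 × 2) + 10 = 20. Prominent incisors would make 21.

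**Events per candidate.**

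| Incidence | Events | 15 candidates | 20 candidates |
|---|---|---|---|
| 10% | 10.6 | 0.71 | 0.53 |
| 15% | 15.9 | 1.06 | 0.80 |
| 20% | 21.2 | 1.41 | 1.06 |

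The ten clinical tests alone have 10.6/10 = 1.1 to 21.2/10 = 2.1 events each. At 10 per term, 15 to 20 terms would need 150 to 200 events: 750 to 1000 women at 20% incidence, or 1500 to 2000 at 10%.

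**Size of the false-positive problem.** With independent candidates and no true effect, the chance that at least one univariate test reaches P<.05 is 1 − 0.95^15 = 54% or 1 − 0.95^20 = 64%.

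Simulation carries this through to the model: 106 women, normally distributed candidates, no true predictor, pairwise correlation 0 or 0.4, incidence 10% to 20%. The share of studies reporting at least one independent predictor at P<.05 was:
- screening on P<.05, then a multivariable fit: about 24% to 61%;
- all 15 or 20 candidates entered: about 54% to 76%.

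Independent runs agree to within sampling error. With all 20 candidates forced in at 10% incidence, separation or non-convergence occurred in 17% to 55% of fits, depending on the assumed effects and correlations.

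**If some candidates do predict.** Assume two to four true predictors, with log odds ratios of 0.5 to 0.8 per SD and correlation 0 or 0.4. After screening and modelling, about 17% to 36% of the selected predictors were false, and the log odds ratios of the true predictors that were selected were inflated about 1.2- to 3.5-fold.

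**The case against.** The strongest reply is that section 3.10 does not describe the procedure under criticism. It puts univariate tests and logistic regression in separate sentences. It does not say that a P value decides entry, or that all candidates go into one model. An entry rule, variable list or cap may well sit in a fuller plan, and their absence from a journal article is no finding. This stands, and the point does not rest on that absence. A fuller plan could supply a selection rule, but it could not supply events: N, incidence, candidate list and objective are fixed here, and both natural readings perform badly.

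Second, section 3.9 speaks of two or more correlates, so two is the floor of that wording and 10 events per term is an interpretation. This also stands, but no reasonable reading stretches 20 events to 15 or 20 terms.

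Third, a reader might infer that whatever the model names will be mostly chance. The documents do not support that. It would require that no measure predicts anything, whereas the Discussion cites earlier evidence that such ultrasound distances do predict difficult airway in non-obstetric patients. Under the moderate true effects assumed above, most selected predictors were real, though exaggerated. Nor should the simulated rates be set against 5% as if the plan had promised familywise control; its P<.05 applies to each test.

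Finally, the main aim, ultrasound against Cormack–Lehane grade, is addressed by group comparisons and ROC curves for each measurement. The logistic model chiefly serves the secondary objective.

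**Conclusion.** The concern holds in this form: the expected events support about one or two model terms, against 15 to 20 candidates, or 0.5 to 1.4 events per candidate. That ratio uses only the article's own figures; the one-or-two limit also needs the 10-per-term reading. Unstable selection, overestimated odds ratios and a substantial chance of false predictors follow under either reading of section 3.10. The range of roughly a quarter to three quarters of studies with at least one false predictor rests on the assumed absence of any true effect and on assumed correlations of 0 to 0.4, neither of which the article gives.

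The event count may also be optimistic. Section 3.7 withdraws women with unanticipated difficult ventilation or intubation, and the Discussion acknowledges possible selection bias from this. The change should be made before analysis. It concerns the secondary objective and does not undermine the ROC analysis of each measurement.

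**What to change.** In section 3.10:

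1. State that univariate P values do not decide entry to the logistic model.
2. Prespecify a small model with the number of terms tied to the observed events, at about one per 10. Name one ultrasound measure (level and neck position) as the first term and, if events allow, one clinical test as the second. At about 11 events only the first term is supported.
3. Fit it with Firth or ridge penalisation.
4. Report the other clinical tests as univariable odds ratios with 95% confidence intervals, or in a penalised model, labelled exploratory in either case and not presented as established independent predictors.

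This needs no new patients or measurements, only revised wording and a routine beyond standard logistic regression. The real cost is scientific: the secondary objective asks about the clinical tests as a group, and it could be answered firmly for only one or two variables. Keeping the full question would take many more events, as the working shows.

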## Discussion

4

The maternal mortality has been reduced over the past four decade, but, the rate of failed tracheal intubation has remained unchanged in obstetrics anesthesia. Parturient have high risk of difficult airway due to the physically airway anatomy changes in the upper respiratory tract. Like obese patients, decreased functional residual capacity and increased oxygen requirements accelerate the onset of desaturation during apnea.^[1]^ In 2015, China's one-child policy was replaced by a universal two-child policy. Sichuan Provincial People's Hospital is the center of clinical service and research, one of National Top Hundred Excellent Hospitals in China. Since 2015, more elderly and critically ill parturient were received in our hospital, and need to cesarean section with general anesthesia. Accurate airway assessment is the first step towards avoiding potential complications and should always be the most important in airway management. Unfortunately, current clinical predictors such as the Mallampati score, thyromental distance had low sensitivity and high variability for detecting a difficult airway. Ultrasound is a high-frequency sound wave, it is bedside, radiation-free, cheap, fast and accurate, is the best choice in obstetric anesthesia. Previous study found that ultrasound distances from the thyroid isthmus to skin surface, the minimum distance from the hyoid bone to skin surface, the minimum distance from skin to anterior commissure of the vocal cords, the minimum distance from skin to trachea at the level of the jugular notch and the distance from skin to epiglottis midway can predict the difficult airway in non-obstetric patients.

This is likely the first study to find whether preoperative ultrasound assessment of neck anatomy can predict difficult airway in parturient. The limitations are,

1)in order to ensure patient safety, patients with unexpected and complicated difficult airway management will be withdrawn from the study, that might cause a potential selection bias.2)this is a single-center observation study in Chinese people, the extrapolation of our findings to other centers and race of people needs further evaluation.

Our study will analysis correlations between ultrasound measurements of anterior cervical soft tissue thickness at five anatomical levels (hyoid bone, epiglottis, cricothyroid membrane, thyroid isthmus and suprasternal notch) in the upper airway, and the Cormack–Lehane grade, to provide a new basis for evaluation of difficult airways and to explore new and more effective methods to address this problem.
